### Process evaluation

The comprehensive process evaluation follows the UK MRC guidance for the process evaluation of complex interventions [47], aiming to identify the context of the intervention delivery, assess implementation and intervention fidelity, identify mechanisms of impact and interpret outcomes in the light of these identified processes. Thus, observed effects can be interpreted in the light of how the intervention actually worked. Methods comprised are qualitative interviews, focus groups, written questionnaires, and extensive documentation of the ongoing research process, based on a pre-specified logic model. A more comprehensive protocol for the process evaluation will be submitted later.

### Health economic evaluation

In consideration of O’Hanlons’ framework on economic evaluations of ACP [48], the objective of the health economic evaluation is to estimate implementation and intervention costs during the study period. Cluster adjustment will be performed. Further, cost implications of the ACP intervention will be explored.

The estimation of (i) implementation und intervention costs will be performed from the perspective of the home care services (on organizational level) as well as the German social insurance system (on patient level). Cost implications of the intervention (ii) during the 12-month follow-up, in particular inpatient care costs (hospital as well as short-term nursing home), expenses for rehabilitation services and medical devices, will be determined from the perspective of the German social insurance system (on patient level). Cost implications of the intervention, which (iii) could be expected in following years and therewith after the end of our study will be explored by using hypothetic scenarios (on patient level). The scenarios were developed according to international literature on ACP [48–51] and pre-tested during the pilot phase prior the STADPLAN study.

For (i) and (ii), costs for implementation- and intervention-related components will be collected during the study. In a first step, resource use associated with ACP implementation and intervention (e.g. ACP facilitators, qualified nurses, time and material) as well as related health care resource use will be assessed during the study. In a second step, resource use will be multiplied by unit costs.

The scenarios, which are used for the calculation of point (iii), describe the goals of care chosen by a random subgroup of 120 study participants on cluster level at baseline and at the end of the study for various hypothetic health events. These goals of care will be transformed into costs in three steps: first, we will identify the healthcare resources required to treat the hypothetic health event; second, the amount of resources has to be determined and third, each resource will be multiplied by unit costs. The difference in treatment costs resulting of the decision made at baseline and at the end of the study will be compared between the intervention and the control group.

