### Randomisation

Randomisation will be carried out on the cluster level (i.e. the home care service) by one investigator ([name]), who is not involved in the recruitment process. Thus, allocation concealment will be guaranteed. Clusters will be allocated 1:1 between intervention and control group. Computer-generated lists will be used with block sizes of two in order to inform the home care services as fast as possible so they can reliably plan time for intervention. Each pair will be allocated simultaneously. Randomisation will be stratified by study site (Oldenburg, Lübeck and Halle (Saale)).

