### Secondary outcomes

The secondary outcomes are the proportion of participants with ADs, self-reported health related quality of life (VR-12 with 12 items) [38, 39], anxiety and depression (HADS with 14 items) [40], number of hospitalisations, proportion of participants being institutionalized, mortality, and ACP engagement with four items on readiness to pass the ACP process [41] (Table 2). Data measurement will be conducted at baseline (t0), after 6 months (t1) and after 12 months (t2). Baseline data will include age, sex, family situation, amount of health care services used, selected comorbidities, hearing capacity, vision, mobility, and functional status. Most of these data will be assessed in face-to-face interviews with the patients at their homes. Data routinely documented by the respective home care services will be collected during visits at the home care service.

**Table 2 Tab2:** Study outcomes/variables, measurement tools and data collection schedule

Outcome/ variable	Measured by	Validated version*	Baseline	6 months (t1)	12 months (t2)	Assessed by
Patient activation (primary outcome)	Patient activation Measure (PAM-13) [42]	German version [36]	✓	✓	✓	RA – at home visit
ACP behaviour	Patient engagement survey [41]	English version [41]	✓		✓	RA – at home visit
Anxiety and depression	Hospital anxiety and depression scale (HADS) [40]	German version [43]	✓		✓	RA – at home visit
Self-reported, health-related quality of life	Veterans Health Administration (VR-12) [38, 39]	German version [44]	✓		✓	RA – at home visit
Deaths, hospitalization, institutionalisation	Own questions	n.a.	✓	✓	✓	RA – at home care service & home visit
Proxy/Family involvement**	Audit of ACP discussion	n.a.	✓			Nurse facilitator
Sociodemographic & clinical data, hearing capacity by RAI-NH [45] & vision	Own questions	n.a.	✓			RA- at home care service & home visit
GPs involvement	Own questions	n.a.	✓	✓	✓	
Physician visits, formal & informal care	Own questions	n.a.	✓		✓	RA – at home visit
Healthcare preferences	Hypothetical scenarios	Adapted German version [46]***	✓		✓	RA – at home visit

*****all instruments were pretested in a German version in the pilot study**; ****intervention group only; ******* adapted version of the Life-Support Preferences Questionnaires and Emanuel Medical Directive, which will be validated in the STADPLAN study within a limited subgroup (*n* = 120); *RA* Research assistant, *RAI-NH* Resident Assessment Instrument for Nursing Homes

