### Data analysis

Data analyses will be conducted by a blinded biometrician (BH), who does not know, which group is intervention or control, following Good Clinical Practice (GCP) standards. All analyses will be cluster-adjusted and follow the intention-to-treat principle.

Baseline characteristics will be displayed descriptively. The primary outcome (PAM-13-D) will be compared between intervention and control group using a mixed model (α = 0.05, two-sided) and adjusted for fixed (baseline values including initial value of PAM-13-D) and random (cluster) effects. For patients who early terminated the study, last observations (information at the last point of measurement) will be carried forward (LOCF imputation). For sensitivity, the same analysis will be performed as complete case analysis without LOCF. Furthermore, a more detailed analysis comparing the longitudinal course of the primary outcome in the interim time points after 6 and 12 months without imputation will be investigated using a mixed model with the intervention and initial PAM-13-D values as fixed effects, clusters as a random effect, and using covariance patterns to adjust for repeated measurement.

Mixed models will also be used for all secondary endpoints, taking into account cluster effects or repeated measurements. Survival analyses will be conducted using stratified Kaplan-Meier curves and Cox regression. Subgroup analyses will be conducted stratified by age and sex.

Economic analyses on patient level will include individual total costs over 12 months. Differences between intervention and control group will be estimated using Gamma regression, again accounting for cluster effects. Adjustment is planned for prematurely dropped out. On organizational level (implementation and intervention costs from the perspective of home care services) descriptive analyses are will be performed.

For the process evaluation, qualitative data (interviews and focus groups) will be summarised and narratively described [53] supported by MAXQDA. Further, quantitative data (questionnaires with closed- and open-ended questions) will be analysed using descriptive statistics.

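### The exploratory scenario-cost comparison is stated as a change score with no stated adjustment for baseline scenario cost: a minor, avoidable loss of precision in a subgroup of 120

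*Protocol article*

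**What the plan says.** Under Health economic evaluation, the third aim concerns costs that might arise after the study ends. The article presents it as something to be explored. The scenario answers come from a "random subgroup of 120 study participants on cluster level at baseline and at the end of the study"; they are converted into costs, and then "The difference in treatment costs resulting of the decision made at baseline and at the end of the study will be compared" between intervention and control.

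Table 2 (Secondary outcomes) lists healthcare preferences, measured by "Hypothetical scenarios", with ticks at baseline and at 12 months. Its footnote says of the adapted instrument "which will be validated in the STADPLAN study within a limited subgroup" and gives n = 120. Each subgroup member should therefore have a baseline scenario cost.

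The Data analysis section names no model for this comparison. For the primary outcome it specifies a mixed model "adjusted for fixed (baseline values including initial value of PAM-13-D) and random (cluster) effects". For patient-level costs over the 12 months it says: "Differences between intervention and control group will be estimated using Gamma regression, again accounting for cluster effects". The scenario costs are in neither sentence, and they are not among the secondary outcomes for which mixed models are promised. Health economic evaluation adds only that the analysis will be adjusted for clustering.

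**The concern.** A between-arm comparison of change fixes the coefficient of the baseline cost at 1. Linear adjustment estimates that coefficient from the data. Unless the true slope of end cost on baseline cost is 1, the change score carries avoidable variance, and a chance difference between arms at baseline moves the estimate.

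This is the only analysis described for costs in later years. It rests on 120 of the 960 participants (one eighth), and clustering reduces its information further. Nothing in the article suggests precision to spare: no power or precision figure is attached to the subgroup.

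**Working it through.** **Figures in the plan.** There is none for this subgroup to reproduce. The only sample-size calculation concerns the primary endpoint. It reproduces and is unaffected: 173 per group by the t-test; design factor 1 + 29 × 0.05 = 2.45; 173 × 2.45 / 30 = 14.13, rounded up to 15 clusters per group; 2 × 15 + 2 = 32 clusters; 32 × 30 = 960.

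**Inputs.** Subgroup of 120 (Health economic evaluation; Table 2 footnote). About 60 per arm is assumed, because "Clusters will be allocated 1:1 between intervention and control group" (Randomisation). The baseline-to-end correlation ρ is not given, so 0.3 to 0.9 is assumed.

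**Variances.** Let s₀ and s₁ be the SDs of scenario cost at baseline and at the end.

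- Change: s₀² + s₁² − 2ρs₀s₁
- Baseline-adjusted (large sample): s₁²(1 − ρ²)
- Change minus adjusted: (s₀ − ρs₁)², which is never negative

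With s₀ = s₁ = 1 these are 2(1 − ρ) and 1 − ρ². Their ratio, change to adjusted, is 2/(1 + ρ). The relative CI width is the square root of that ratio. The equivalent number of adjusted participants is 120(1 + ρ)/2. The detectable difference (80% power, two-sided 5%, 60 per arm, no clustering, in SD units) is (1.960 + 0.842) × √(2 × variance / 60).

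| ρ | Variance: change | Variance: adjusted | Ratio | CI wider by | 120 by change score worth | Detectable: change | Detectable: adjusted |
|---|---|---|---|---|---|---|---|
| 0.3 | 1.40 | 0.91 | 1.54 | 24% | 78 | 0.605 | 0.488 |
| 0.5 | 1.00 | 0.75 | 1.33 | 15% | 90 | 0.511 | 0.443 |
| 0.7 | 0.60 | 0.51 | 1.18 | 8% | 102 | 0.396 | 0.365 |
| 0.9 | 0.20 | 0.19 | 1.05 | 3% | 114 | 0.229 | 0.223 |

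A comparison of end costs alone has variance 1. Below ρ = 0.5 the change score is therefore less precise than ignoring baseline.

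**Clustering.** Simulation of 120 participants as 30 clusters of 4, 12 of 10 and 4 of 30 (ICC 0.05, same ρ within and between clusters) gave ratios of 1.54–1.55, 1.29–1.33, 1.16–1.19 and 1.04–1.05 for the four values of ρ. Clustering lowers the precision of both methods but leaves the ratio nearly unchanged.

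**Unequal variances.** The loss vanishes when ρs₁/s₀ = 1. For example, with ρ = 0.7 and s₁/s₀ = 1/0.7 = 1.43, change is 1 + 2.04 − 2.00 = 1.04 and adjusted is 2.04 × 0.51 = 1.04. It grows when the end SD is smaller than the baseline SD. With ρ = 0.5 and an assumed s₁/s₀ = 0.7, change is 1 + 0.49 − 0.70 = 0.79 and adjusted is 0.49 × 0.75 = 0.3675. The ratio is 2.15 and the CI is 47% wider.

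**Chance imbalance.** Given an observed baseline difference d, the change score is shifted by (1 − ρ)d in the opposite direction (equal variances). With 60 per arm and no clustering, the SE of d is √(2/60) = 0.18 SD. At ρ = 0.5, a one-SE imbalance shifts the estimate by 0.5 × 0.18 = 0.09 SD.

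**The case against.** The strongest reply is that the article names the quantity compared but not the model. A linear model of the change with baseline cost as a covariate fits the sentence and gives exactly the same arm effect as adjusting the end cost. A fuller plan may specify that. This stands in part: the article does not rule adjustment out. But it does name the contrast, and its plain reading is an unadjusted comparison of change. No other sentence repairs it. The Gamma model is tied to 12-month costs and could not be fitted to a difference that may be zero or negative.

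The second reply also stands: the analysis is exploratory, no test or precision target is attached to it, and the loss is trivial if preferences are stable.

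Three stronger readings are tempting and are not supported:

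- A reader might infer that the cost analysis breaks a trial-wide rule of baseline adjustment. The article states adjustment for the initial value for PAM-13-D only. The sentences on secondary endpoints and on 12-month costs name no baseline covariate.
- A reader might infer that the comparison is biased. Under randomisation it is unbiased on average; the imbalance shift is conditional on the baseline difference observed.
- A reader might take one figure, such as 120 participants being worth 90, as a fact about this trial. It is one assumed point: ρ = 0.5 with equal variances.

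**Conclusion.** The point holds as a minor efficiency improvement. The article states a change-score comparison of scenario costs, the baseline cost is available, and no adjustment for it is stated. In large samples linear baseline adjustment is never less precise. With equal variances and ρ from 0.3 to 0.9, the stated comparison gives a confidence interval about 24% down to 3% wider. The actual loss in this trial cannot be determined, because neither ρ nor the variance ratio is documented, and it could be nil. The comparison is valid as it stands, and the primary analysis and sample size are not touched.

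**What to change.** Add one sentence: the arm difference in scenario costs will be estimated in a cluster-adjusted linear model of end-of-study scenario cost (or, equivalently, of the change) with the participant's baseline scenario cost as a covariate; mean change per arm will be reported descriptively.

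The cost is one degree of freedom for the baseline slope, negligible with 120 participants. No new data are needed.

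Site terms are not needed for this gain. The article does not say how many home care services supply the 120. If whole services of about 30 were drawn, there would be 120 / 30 = 4 clusters, and an intercept, an arm term and two site terms would use up all the between-cluster information. Site should therefore be left out if the clusters are few. The gains shown above apply to linear adjustment and should not be assumed for a generalised linear model.

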### Sample size

To detect an effect size of 0.35 (Cohens d), which corresponds to a medium effect, with respect to the primary endpoint after 12 months between the intervention and the control group with 90% power (β = 0.10) using a two-sided significance level of 5% (α = 0.05) based on the t-test, a non-cluster study setting would require a total of 173 patients per group. Taking cluster sampling into account [52], we used an intra-cluster correlation coefficient (ICC) of 0.05 in accordance with a study on the effectiveness of ACP in the Netherlands of Korfage et al. [20]. Assuming an average cluster size of 30 participants per home care service, the design factor is 2.45 and 15 clusters are required per group. Estimating that two home care services might drop out [21], 32 clusters with a total of 960 participants will be included in the study.

### Data analysis

Data analyses will be conducted by a blinded biometrician (BH), who does not know, which group is intervention or control, following Good Clinical Practice (GCP) standards. All analyses will be cluster-adjusted and follow the intention-to-treat principle.

Baseline characteristics will be displayed descriptively. The primary outcome (PAM-13-D) will be compared between intervention and control group using a mixed model (α = 0.05, two-sided) and adjusted for fixed (baseline values including initial value of PAM-13-D) and random (cluster) effects. For patients who early terminated the study, last observations (information at the last point of measurement) will be carried forward (LOCF imputation). For sensitivity, the same analysis will be performed as complete case analysis without LOCF. Furthermore, a more detailed analysis comparing the longitudinal course of the primary outcome in the interim time points after 6 and 12 months without imputation will be investigated using a mixed model with the intervention and initial PAM-13-D values as fixed effects, clusters as a random effect, and using covariance patterns to adjust for repeated measurement.

Mixed models will also be used for all secondary endpoints, taking into account cluster effects or repeated measurements. Survival analyses will be conducted using stratified Kaplan-Meier curves and Cox regression. Subgroup analyses will be conducted stratified by age and sex.

Economic analyses on patient level will include individual total costs over 12 months. Differences between intervention and control group will be estimated using Gamma regression, again accounting for cluster effects. Adjustment is planned for prematurely dropped out. On organizational level (implementation and intervention costs from the perspective of home care services) descriptive analyses are will be performed.

For the process evaluation, qualitative data (interviews and focus groups) will be summarised and narratively described [53] supported by MAXQDA. Further, quantitative data (questionnaires with closed- and open-ended questions) will be analysed using descriptive statistics.

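### Study site stratifies the randomisation but is not named in the primary PAM-13-D model and is absent from the longitudinal model's listed fixed effects, so the test is conservative to the extent that sites differ

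*Protocol article*

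**What the plan says.** The Randomisation section of the protocol article makes the home care service the unit of allocation. It states: "Clusters will be allocated 1:1 between intervention and control group". On method: "Computer-generated lists will be used with block sizes of two", with both members of a pair allocated at the same time. On stratification: "Randomisation will be stratified by study site (Oldenburg, Lübeck and Halle (Saale".

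The Data analysis section describes two models for PAM-13-D:

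- The primary model is a mixed model, "adjusted for fixed (baseline values including initial value of PAM-13-D) and random (cluster) effects".
- The longitudinal model covers 6 and 12 months without imputation. It is fitted "using a mixed model with the intervention and initial PAM-13-D values as fixed effects, clusters as a random effect", with covariance patterns for the repeated measurements.

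Neither description mentions study site, and no other section says that the stratification factor enters an analysis. The baseline data listed under Secondary outcomes are patient characteristics such as age, sex, comorbidities and functional status. Site is not among them.

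**The concern.** Pairwise allocation within site places equal numbers of intervention and control clusters at each site, so site-level differences cancel from the treatment contrast. A model without site does not know this. It treats those differences as ordinary cluster-to-cluster variation and charges them to the standard error. The design then gains precision that the analysis does not report.

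Site differences are plausible: two sites lie in north-western Germany and one in eastern Germany. With 16 clusters per arm, the between-cluster variance carries much of the uncertainty. At stake are the width of the confidence interval and some power. Bias and an inflated false-positive rate are not.

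**Working it through.** **Inputs from the article (Sample size section).** Effect size d = 0.35, 90% power, two-sided 5% level, ICC 0.05, 30 participants per cluster, 15 clusters required per group, 32 clusters and 960 participants recruited.

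**Input not in the article.** The share x of the between-cluster variance that is due to site is assumed, over a range from 0% to 50%.

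**1. The plan's own figures reproduce.**
- A two-sample t-test at d = 0.35 needs 173 per group (power 90.1%).
- Design factor: 1 + 29 × 0.05 = 2.45.
- 173 × 2.45 / 30 = 14.13, rounded up to 15 clusters per group.
- 2 × 15 + 2 = 32 clusters, and 32 × 30 = 960.

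**2. Closed form, 32 clusters of 30.** Total variance is set to 1.
- Cluster-mean variance with site left in: v0 = 0.05 + 0.95/30 = 0.0817.
- With site removed: v1 = 0.05(1 − x) + 0.95/30.
- The standard error without site is too large by the factor √(v0/v1).
- Tests use t with 30 df (site omitted) and 28 df (site included). Power is from the noncentral t.

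| Assumed site share x | v1 | √(v1/v0) | SE too large by | Type I error, site omitted | Power, site omitted | Power, site included |
|---|---|---|---|---|---|---|
| 10% | 0.0767 | 0.969 | 3% | 4.4% | 92.4% | 93.2% |
| 30% | 0.0667 | 0.904 | 11% | 3.1% | 93.7% | 95.9% |
| 50% | 0.0567 | 0.833 | 20% | 2.0% | 95.0% | 98.0% |

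A simulation with the three site effects held fixed (32 clusters, 40,000 runs) agrees. Type I error without site is 4.1%, 3.0% and 1.8%, and each power is within 0.3 points of the table.

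**3. Simulation with site effects drawn at random.** There were 40,000 runs per setting, equal cluster sizes and arms balanced within site. The number of clusters per site is assumed (10/10/10 for 30 clusters, 10/10/12 for 32).

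| Site share | SE too large by (30 clusters) | Type I error, site omitted (30 clusters) | Power, omitted → included (30 clusters) | Power, omitted → included (32 clusters) |
|---|---|---|---|---|
| 0% | none | 5.1% | 89.9% → 89.7% | 91.8% → 91.7% |
| 10% | 1% | 4.6% | 90.7% → 91.3% | 92.8% → 93.4% |
| 25% | 5% | 3.7% | 92.0% → 93.6% | 93.9% → 95.3% |
| 50% | 14% | 2.8% | 94.3% → 97.3% | 95.7% → 98.0% |

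With site included, type I error lies between 4.7% and 5.1%.

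**4. Why the two sets differ.** Three site effects drawn at random with a given variance spread around their own mean by only (3 − 1)/3 of that variance on average. Less of it therefore reaches the estimated cluster variance than in the closed form, which puts in the full share. The two approaches agree on direction and order of size.

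**5. What is not modelled.** Neither calculation includes baseline PAM-13-D. Both hold the total ICC at 0.05, so a larger site share means less variance within sites. That is why power rises down each table even when site is omitted.

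**The case against.** The case on the other side is substantial.

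- **The primary model's list is open.** A reader might infer that site is excluded from the primary analysis. The text does not support that: the covariates are baseline values that include initial PAM-13-D, site is known at baseline, and an article may leave the full list to an analysis plan. What remains is that site is not named, and that a recruiting centre is not the natural reading of a patient's baseline value.
- **The longitudinal description may be condensed.** It names no time term either, although its purpose is to compare the course at 6 and 12 months. It is also a supplementary analysis. This weakens the inference that site was deliberately dropped, but the fixed effects as listed do leave it out.
- **The harm is conditional.** A reader might conclude that the standard error is overstated and power is lost as a matter of fact. That holds only if sites still differ in 12-month PAM-13-D after baseline adjustment, which the article does not quantify. Stable regional differences would show at baseline and be partly absorbed by the planned adjustment, so the calculated effects probably lean high.
- **The consequence is conservative.** There is no bias and no inflated error rate, and the planned 90% power is met or nearly met in every scenario.

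All four points stand and limit the finding. They do not remove the reason to name the stratification factor, because adding it costs almost nothing.

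**Conclusion.** The point holds as a modest, conditional improvement. Site stratifies the allocation, is not named in the primary PAM-13-D model, and is missing from the fixed effects listed for the longitudinal model. To the extent that sites differ after baseline adjustment, the interval is too wide and the test conservative.

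For assumed site shares of 10% to 50% of the between-cluster variance, the standard error is about 1% to 20% too large, depending on how site effects are modelled. Type I error runs from about 4.6% down to about 2%, and about 0.6 to 3 points of power are lost. With no site differences nothing is lost. These figures rest on the planning ICC of 0.05, equal clusters of 30, exact balance within site and no baseline covariate.

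The documents do not support calling the trial underpowered or its primary test invalid: power without site is 89.9% or higher in every setting calculated. Nor do they show that site is left out of the secondary or survival models. The article gives no covariate list for those, and it does not say what the Kaplan-Meier curves are stratified by.

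**What to change.** State in the Data analysis section that study site (three levels) is a fixed effect in both the primary and the longitudinal PAM-13-D model, alongside initial PAM-13-D and the random cluster effect. Carry it into the secondary mixed models for consistency. Fix this before the analysis, so that the open covariate list leaves no choice about site.

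The cost is one sentence and 2 of about 30 cluster-level degrees of freedom. If sites do not differ, that is about 0.2 points of power (89.9% to 89.7% with 30 clusters). If they do, the test returns to about its nominal level and the lost power is recovered. No change to the design or data collection is needed.
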